## Abstract

**Background:**

Doublet chemotherapy in combination with a biologic agent has been a standard of care in patients with metastatic colorectal cancer for over a decade. The evidence for a “lighter” treatment approach is limited to mono-chemotherapy plus bevacizumab in the *RAS* unselected population. Anti-EGFR antibodies have activity as monotherapy or in combination with chemotherapy in *RAS* wildtype metastatic colorectal cancer; however their role in first-line treatment in combination with 5-fluorouracil monotherapy or when given alone has not been well studied. MONARCC aims to investigate this approach in an elderly population.

**Methods/design:**

MONARCC is a prospective, open-label, multicentre, non-comparative randomised phase II trial. Eligible patients aged ≥70 with unresectable metastatic, untreated, *RAS*/*BRAF* wildtype metastatic colorectal cancer will be randomised 1:1 to receive panitumumab alone or panitumumab plus infusional 5-fluorouracil. *RAS* and *BRAF* analyses will be performed in local laboratories. Comprehensive Health Assessment and Limited Health Assessments will be performed at baseline and at 16 weeks, respectively, to assess frailty. The Patient Symptom Questionnaire and Overall Treatment Utility are to be undertaken at different timepoints to assess the impact of treatment-related toxicities and quality of life. Treatment will be delivered every 2 weeks until disease progression, unacceptable toxicity (as determined by treating clinician or patient), delay of treatment of more than 6 weeks, or withdrawal of consent. The primary end point is 6-month progression-free survival in both arms. Secondary end points include overall survival, time to treatment failure, objective tumour response rate as defined by RECIST v1.1 and safety (adverse events). Tertiary and correlative endpoints include the feasibility and utility of a comprehensive geriatric assessment, quality of life and biological substudies.

**Discussion:**

MONARCC investigates the activity and tolerability of first-line panitumumab-based treatments with a view to expand on current treatment options while maximising progression-free and overall survival and quality of life in molecularly selected elderly patients with metastatic colorectal cancer.

**Trial registration:**

Australia New Zealand Clinical Trials Registry: ACTRN12618000233224, prospectively registered 14 February 2018.

**Supplementary Information:**

The online version contains supplementary material available at 10.1186/s12885-021-08644-4.

## Background

Doublet chemotherapy (e.g., FOLFOX or FOLFIRI) in combination with a biologic agent (anti-EGFR or anti-VEGF) are established first-line treatments against metastatic colorectal cancer (mCRC) [1, 2]. In patients with *KRAS* exon 2 wildtype mCRC, the use of anti-EGFR antibodies with doublet chemotherapy in the first-line setting has demonstrated superior overall survival (OS) compared with bevacizumab with doublet chemotherapy or doublet chemotherapy alone [1–3]. Subsequent studies have established the benefit of adding anti-EGFR antibodies to first-line doublet therapies is also limited to tumours without mutations in other RAS exons [4, 5]. Therefore, anti-EGFR antibodies are only indicated in patients with no *KRAS* or *NRAS* mutations in exons 2, 3 or 4, which accounts for approximately 40–50% of cases of mCRC. In addition, in patients with *RAS* wildtype disease, the benefit derived from anti-EGFR antibodies is far greater in left-sided than right-sided primary tumours [6, 7]. Approximately 10% of mCRC harbour activating mutations in *BRAF V600E* which are mutually exclusive with *RAS* mutations [8]. Anti-EGFR antibodies have limited, if any activity against *BRAF V600E* mutant cancers, unless combined with a *BRAF* inhibiting agent [9–11]. Therefore, easily determined predictive biomarkers exist to enable selection of patients for treatment with anti-EGFR antibodies.

Patients with mCRC seen in daily practice are often elderly, or have co-morbidities putting them at risk of greater toxicity with standard doublet or triplet regimens than typical populations enrolled onto clinical trials. In addition, some patients have low volume metastases with no or few symptoms. All these patients might be more suited to a “lighter” first-line treatment approach. In elderly patients, number of clinical trials have evaluated such a “lighter” approach in mCRC. AVEX was an open-label phase III randomised control trial that assigned 280 patients aged ≥70 years with untreated, unresectable mCRC to receive capecitabine alone or capecitabine plus bevacizumab. The addition of bevacizumab resulted in an improvement in progression-free survival (PFS) from 5.1 to 9.1 months (HR 0.53; *p* < 0.0001), but OS was not statistically different (HR 0.79; *p* = 0.18) between the two arms. The combination of bevacizumab and capecitabine was well tolerated. However, quality of life and geriatric specific assessments were not performed [12]. The AGITG MAX phase III trial evaluated capecitabine, capecitabine plus bevacizumab, and capecitabine, bevacizumab plus mitomycin as first-line treatment in *RAS* unselected, unresectable treatment naive mCRC. Ninety-nine patients (21%) were identified as age ≥ 75 years in the geriatric subgroup analysis. The PFS benefit derived from the addition of bevacizumab to capecitabine in the elderly population was similar to that in the intention-to-treat population and those < 75 years. There was no signal for increased toxicity in the elderly subgroup [13], supporting the rationale for adding bevacizumab to single-agent chemotherapy in elderly patients.

The effect of age on the efficacy and safety of an anti-EGFR antibody together with doublet chemotherapy were evaluated in subgroup analyses of the PRIME and CRYSTAL trials. Post hoc analysis of the PRIME trial evaluated the effect of age on the efficacy and safety of FOLFOX4 with panitumumab versus FOLFOX4 alone as a first-line treatment in patients with RAS wildtype mCRC. The older age group was defined as those ≥65 years and represented 38% of the participants. Addition of panitumumab to FOLFOX4 was well tolerated and was associated with a trend to increased efficacy in patients aged ≥65 years in terms of PFS (9.7 vs 9.2 months, HR 0.88, 95%CI 0.65–1.19) and OS (26.4 vs 17.4 months HR 0.80, 95%CI: 0.58–1.09). However, there were too few patients aged ≥75 (*n* = 34) to enable firm conclusions to be drawn [14].

Similarly, in the subgroup analysis of the CRYSTAL trial, older age group was defined as ≥65 years and represented about 30% of participants. Addition of cetuximab to FOLFIRI chemotherapy led to a similar improvement in PFS (older group: HR 0.56; 95%CI 0.31–1.03; younger group: HR 0.55; 95%CI 0.38–0.81) and OS (older group: HR 0.91; 95%CI 0.60–1.38; younger group: HR 0.61; 95%CI 0.45–0.82), respectively. However, patients in the older age group had a higher incidence of grade 3–4 treatment-related adverse events compared to the younger age group (77% vs 66.7%, respectively) [15]. The results demonstrated that while elderly patients derived similar survival benefit from anti-EGFR antibodies plus doublet chemotherapy compared to the younger population, this may be associated with higher rates of toxicity.

Studies conducted some years ago have generally found that single-agent chemotherapy results in lower response rates and shorter PFS compared to doublet therapy, but no difference in OS was found when sequencing through second and later-line options was planned [16]. Findings were similar when bevacizumab was added [17]. This lack of evidence of OS benefit with combination chemotherapy has opened the opportunity to investigate treatment de-intensification in the elderly in order to reduce treatment-related toxicity.

The Spanish Cooperative Group for the Treatment of Digestive Tumours (TTD) has conducted a number of studies evaluating the safety and activity of anti-EGFR as monotherapy or in combination with single-agent chemotherapy. In a single-arm phase 2 study, 41 patients aged ≥70 years with untreated mCRC with positive tumour tissue immunohistochemistry for EGFR were treated with single-agent cetuximab. Except for skin toxicities, less than 5% of patients had grade 3 or 4 adverse events. The median time to progression and OS in the intention-to-treat population were 2.9 months and 11.1 months, respectively [18]. A subsequent single-arm phase 2 trial investigated single-agent panitumumab in 33 patients aged ≥70 years with *KRAS* (exon 2) wildtype mCRC. In the subgroup of patients with extended *RAS* wildtype, the median PFS and OS were 7.9 months and 12.3 months, respectively [19]. Cetuximab plus capecitabine was evaluated in a single-arm phase 2 study which recruited 66 *RAS* unselected patients aged ≥70 years. The median PFS and OS of patients with *KRAS* (exon 2) wildtype disease were 8.4 months and 18.8 months, respectively. Cetuximab plus capecitabine also appeared to be less toxic compared with doublet chemotherapy [20]. Even though these studies did not use all the predictive biomarkers we have today, the results suggest that anti-EGFR antibody plus mono-chemotherapy might be a reasonable alternative to more aggressive regimens in the elderly population.

Most recently, the PANDA study was presented in abstract form. This phase 2 study randomised 185 patients aged ≥70 years with untreated wildtype *RAS* and *BRAF* mCRC to receive FOLFOX plus panitumumab or 5-fluorouracil (5-FU) plus panitumumab. The median age of 77 years in both arms is similar to that in other studies investigating an elderly population. The geriatric assessment G8 score was prospectively collected and used as a stratification factor. The primary endpoint of PFS was reached in each arm, at 9.6 months (95% CI 8.8–10.9, *p* < 0.001) and 9.1 months (95% CI 7.7–9.9, *p* < 0.001) in the FOLFOX-panitumumab and the 5-FU-panitumumab arms, respectively. The overall response rate and disease control rate were similar, and the 5-FU plus panitumumab arm had a lower incidence of toxicities. The results demonstrated panitumumab plus mono-chemotherapy is clinically active and well tolerated. However, as chemotherapy was used in both treatment arms, the efficacy of panitumumab monotherapy could not be evaluated [21]. Taken together, these data support further investigation of anti-EGFR antibodies as components of less intensive treatment regimens for elderly patients with untreated *RAS* and *BRAF* wildtype mCRC. A summary of selected studies investigating anti-EGFR antibodies in elderly patients with untreated mCRC is presented in Table 1.

**Table 1 Tab1:** Selected studies involving anti-EGFR antibodies in elderly patients with mCRC

Study	Design	Population	Treatment	Sample size	Primary endpoint	Key Results
Sastre, 2011 [18]	Prospective single arm, phase II.	Patients aged ≥70 with unselected mCRC	Cetuximab monotherapy	41	Overall response rate (ORR)	ORR 14.6% (95% CI 5.6–29.2)
Sastre, 2012 [20]	Prospective, Single arm, phase II	Patients aged ≥70 with unselected mCRC	Cetuximab plus capecitabine	66	Overall response rate (ORR)	ORR 31.8% (95% CI 20.9–44.4) 29 patients had KRAS wild-type disease: response rate 48.3% (95% CI 29.4–67.5),
Sastre, 2015 [19]	Prospective, Single arm, phase II	Patients aged ≥70 with RAS wild-type mCRC	Panitumumab monotherapy	33	PFS at 6 months	6-month PFS rate 36.4% (95% CI 20.0–52.8)
Kinele, 2018 [22]	Prospective, open label randomised phase II	Patients > 75 years, or patients ≥70 years with at least one adverse factor	Cetuximab monotherapy; cetuximab plus capecitabine	24	PFS at 12 weeks	PFS at 12 weeks: monotherapy arm 55% (95% CI 23–83); combination arm 69%; 95% CI 39–91)
Lonadi, 2019 (abstract) [21]	Prospective, open label randomised phase II	Patients aged ≥70 years with *RAS*-*BRAF* wt mCRC	5FU/LV plus panitumumab; FOLFOX plus panitumumab	185	PFS in both arms	Median PFS: FOLFOX-pan 9.6 m (95% CI 8.8–10.9); 5FU/LV-pan 9.1 m (95% CI 7.7–9.9). Response rate: FOLFOX-pan 65%; 5FU/LV-pan 57%

In this article, we describe the study protocol of MONARCC, a randomised phase II study of panitumumab monotherapy and panitumumab plus 5-FU as first-line therapy for *RAS* and *BRAF* wildtype metastatic colorectal cancer. Importantly, infusional 5-FU was chosen as the partner chemotherapy regimen, given the overlapping toxicities between capecitabine and anti-EGFR antibodies as well as the lack of additional efficacy when anti-EGFR antibodies are added to capecitabine-based regimens [23]. The trial is a collaboration between the Australasian Gastrointestinal Trials Group (AGITG) and the National Health and Medical Research Council (NHMRC) Clinical Trials Centre, University of Sydney, Australia.

## Methods/design

### Aim

MONARCC aims to determine the activity of an anti-EGFR monotherapy in a molecularly selected, hitherto under-investigated, but prevalent elderly patient population. This study investigates a tailored first-line strategy aiming to maximise PFS and OS with acceptable toxicity in a *RAS*/*BRAF* wildtype elderly population suitable for treatment with panitumumab or panitumumab plus infusional 5-fluorouracil (5-FU).

### Design

*MONARCC* is a prospective, non-comparative randomised phase II, open-label multicentre clinical trial in which patients with histologically confirmed *RAS* and *BRAF* wildtype untreated metastatic colorectal adenocarcinoma are randomised 1:1 ratio to either panitumumab monotherapy (Arm A) or panitumumab plus infusional 5-FU as per the De-Gramont schedule (Arm B). All treatments are to be administered until disease progression, unacceptable toxicity (as determined by treating clinician or patient), treatment delays of longer than 6 weeks, or withdrawal of consent (Fig. 1). Randomisation will be performed centrally using the method of minimisation where patients will be stratified on performance status (Eastern Cooperative Oncology Group [ECOG] 0, 1 vs 2), site of primary tumour (left vs right), number of metastatic sites (1 vs > 1) and treating institution. Left-sided tumour is defined as at, or distal to, the splenic flexure. All patient will receive doxycycline or minocycline 50–100 mg once a day commencing on Cycle 1 Day 1 for a minimum of 6 weeks as a pro-active approach in managing skin toxicity from panitumumab. MONARCC incorporates a number of patient questionnaires and a Comprehensive Health Assessment (CHA) is conducted at baseline. During therapy, patients complete symptom Patient Symptom Questionnaire (PSQ) and Limited Health Assessment Questionnaire (LHA). Overall Treatment Utility (OTU) is also evaluated. This is a novel endpoint using a composite of clinical and radiological response, toxicity, adverse events and patient response when asked to reflect if treatment has been worthwhile. CHA, LHA, PSQ and OTU were originally developed and used in the MRC FOCUS2 study, based on validated and published questionnaires (Additional file 1) [24]. A list of participating centres is provided in Table 2.

### Study endpoints

The primary end point is 6-month PFS in each arm, defined as the interval from date of registration/randomisation to the date of first evidence of disease progression. Disease progression is defined according to RECIST v1.1 [22], as assessed by the investigators.

Secondary objectives of this study are OS, time to treatment failure, objective tumour response rate (according to RECIST v1.1) and safety profile (rates of adverse events per CTCAE v4.03). Time to treatment failure is defined as time from randomisation to recorded discontinuation of treatment for any reason, including disease progression, treatment toxicity and death.

The tertiary and correlative objectives are exploratory comparisons between the treatment arms including, but not limited to, depth of tumour response and early tumour shrinkage, OS and PFS, OTU, feasibility and utility of a comprehensive geriatric assessment using the CHA and LHA questionnaires, quality of life, physical activity measured by an activity tracking device and correlated with other health related parameters, validation of a prognostic nomogram and study associations between clinical outcomes and potential predictive/prognostic biomarkers.

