### Statistical considerations

The primary endpoint, PFS at 6 months in each treatment arm, will be assessed to determine if these protocols are reasonable alternatives to current standard therapy of capecitabine and bevacizumab. The expected PFS rate is approximately 73% in *RAS*/*BRAF* wildtype tumours in prior studies of capecitabine and bevacizumab. Using the method of Mehta-Cain, a total planned sample size of 80 patients, with 40 patients in each group, would include the upper 95% one-sided confidence interval for the proportion of patients who have not progressed at 6 months, including 73% if more than 23 patients are progression-free at 6 months in either group.

The analysis of PFS at 6 months and OS will be estimated using the method of Kaplan-Meier. Analysis of efficacy endpoints will be undertaken in the final analysis, and there is no planned interim analysis.

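### The primary endpoint, called PFS, is defined by progression alone; death is not an event, so the 6-month rate can be overstated

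*Protocol article*

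**What the plan says.** The Study endpoints section gives the primary endpoint as 6-month PFS in each arm, "defined as the interval from date of registration/randomisation to the date of first evidence of disease progression". The next sentence fixes what progression means: "Disease progression is defined according to RECIST v1.1 [22], as assessed by the investigators". Neither sentence mentions death, and no other section adds it as a PFS event or says how a death without progression is handled.

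Statistical considerations carries the same idea into the decision rule. The quantity for which the confidence limit is computed is "the proportion of patients who have not progressed at 6 months". It is set against an expected PFS rate of about 73% for capecitabine and bevacizumab, with 40 patients per arm and a requirement that more than 23 be progression-free. The stated estimator is Kaplan-Meier.

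Time to treatment failure, defined in the same section, runs to "recorded discontinuation of treatment for any reason, including disease progression, treatment toxicity and death".

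**The concern.** PFS ordinarily takes the first of progression or death. A definition that stops at RECIST progression is time to progression under a PFS label. It leaves two ways to treat a patient who dies without documented progression before 6 months: censor at death in the Kaplan-Meier analysis, or count as not progressed in the 24-of-40 rule. Both move the estimate upward and neither can move it downward, so any error favours declaring a regimen a reasonable alternative to the current standard.

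Such deaths are plausible in this trial. Patients are at least 70 years old with ECOG status up to 2. Only a life expectancy under 3 months is excluded, while the endpoint is read at 6 months. Imaging is every 8 weeks, so a patient can die between scans.

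**Working it through.** **Inputs from the article (Statistical considerations).** n = 40 per arm; benchmark 73%; one-sided 95% upper limit; rule: more than 23, i.e. at least 24, progression-free at 6 months.

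**Step 1: reproduce the plan's threshold.** The exact upper limit for x successes out of n is the 0.95 quantile of a Beta(x + 1, n − x) distribution.

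- x = 23: Beta(24, 17) gives 0.7082, which excludes 0.73.
- x = 24: Beta(25, 16) gives 0.7306, which includes 0.73.

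The stated rule is therefore reproduced exactly, and it turns on a single patient.

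**Step 2: effect of one uncounted death at the boundary.** Take an arm with 23 patients alive and progression-free, 16 progressed and 1 dead without progression.

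- Death counted as an event: 23/40 = 0.575; the rule is not met.
- Death counted as not progressed: 24/40 = 0.600; the rule is met.
- Death censored in Kaplan-Meier: the estimate lies between 23/39 = 0.590 (death before every progression) and 24/40 = 0.600 (death after every progression).

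One death thus reverses the conclusion under the count. Under censoring it pushes the same way by slightly less, depending on when the death occurs.

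**Step 3: effect on the chance of meeting the rule.** Let p be true PFS at 6 months (progression or death as the event) and d the share of an arm that dies without documented progression by then. The article gives neither; d from 0.025 to 0.10 (1 to 4 of 40 patients) is an assumption.

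- Deaths counted as not progressed: apparent rate = p + d.
- Deaths censored, constant cause-specific hazards: apparent rate = exp{ln(p) × [1 − d/(1 − p)]}.
- Chance of meeting the rule = P(X ≥ 24) for X binomial with n = 40 and the apparent rate.

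Example with p = 0.55 and d = 0.05. Censored: exp{ln(0.55) × [1 − 0.05/0.45]} = 0.588, chance 0.505. Counted: 0.55 + 0.05 = 0.60, chance 0.568. With death counted as an event the chance is 0.319.

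| True PFS | Chance, death as event | Apparent rate, censored | Chance, censored | Apparent rate, counted | Chance, counted |
|---|---|---|---|---|---|
| 0.50 | 0.134 | 0.518–0.574 | 0.189–0.436 | 0.525–0.600 | 0.215–0.568 |
| 0.55 | 0.319 | 0.569–0.628 | 0.407–0.706 | 0.575–0.650 | 0.440–0.798 |
| 0.60 | 0.568 | 0.619–0.682 | 0.665–0.898 | 0.625–0.700 | 0.691–0.937 |

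Ranges run from d = 0.025 to d = 0.10. The censored columns match the stated estimator and should be read first. They are approximate, because they apply a binomial count rule to a rate derived under constant hazards.

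**The case against.** The strongest reply is that this is condensed drafting. The article uses the name progression-free survival throughout, and a dead patient is not naturally called progression-free. The sentence is loose in another way too, since it defines a 6-month rate as an interval. The full protocol is not shown and may include death. That may be so, and it means the article cannot establish that the trial will be analysed as time to progression. It does not rescue the printed sentence, which is a stated definition of the primary endpoint and not a detail left to a later document. If death was always meant to count, the sentence misstates the endpoint and needs the same correction.

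Several stronger readings are tempting, and the article does not support them.

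- *Death was left out on purpose, because time to treatment failure names it.* That endpoint is discontinuation for any reason, so a list of reasons is its normal form. The contrast shows the omission but proves no intent.
- *The estimate will be overstated.* This happens only if someone dies without documented progression within 6 months. The article gives no such rate, and the 3-month life-expectancy exclusion, the organ-function criteria and the 8-weekly scans all limit it.
- *The comparison with 73% is unlike for like.* The article calls that figure a PFS rate but does not give the event definition behind it. A mismatch is likely but not shown.
- *The population is frail.* Frailty is something that the trial assesses; it is not an entry criterion.
- *Deaths will be censored, or will count as successes.* No rule for deaths is stated; both treatments are inferred from the literal definition.

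**Conclusion.** The point stands as a definitional error in the primary endpoint. As printed, the event is RECIST v1.1 progression only, and the decision rule repeats that wording. Any resulting bias is upward, and at the boundary a single uncounted death can change an arm's conclusion under the count rule.

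The size is illustrative. With 2.5–10% of patients dying without documented progression and a true PFS of 55%, the chance of passing rises from 32% to about 41–71% with deaths censored, or 44–80% with deaths counted as not progressed. Both the death rate and the true PFS are assumptions. The conclusion that the definition must be corrected does not depend on them, and it makes no claim about what the unseen protocol or analysis plan says.

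**What to change.** Define PFS as the time from randomisation to first RECIST v1.1 progression, as assessed by the investigator, or death from any cause, whichever comes first. Word the decision rule as the number of patients alive and progression-free at 6 months, so that a death by 6 months is a failure. Check that the full protocol and analysis plan say the same, and because the trial is open-label, date any correction before the efficacy analysis.

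The cost is small. It takes one sentence in the endpoint definition and a few words in the rule. OS is already a secondary endpoint, so deaths are needed anyway. The 40 patients per arm and the threshold of 24 stay as they are, because the benchmark is already called a PFS rate. The only downside is that the reported 6-month rate may be slightly lower.
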